## Abstract

**Background:**

Internet-based self-help is an effective preventive intervention for highly prevalent disorders, such as depression and anxiety. It is not clear, however, whether it is necessary to offer these interventions with professional support or if they work without any guidance. In case support is necessary, it is not clear which level of support is needed. This study examines whether an internet-based self-help intervention with a coach is more effective than the same intervention without a coach in terms of clinical outcomes, drop-out and economic costs. Moreover, we will investigate which level of support by a coach is more effective compared to other levels of support.

**Methods:**

In this randomized controlled trial, a total of 500 subjects (18 year and older) from the general population with mild to moderate depression and/or anxiety will be assigned to one of five conditions: (1) web-based problem solving through the internet (self-examination therapy) without a coach; (2) the same as 1, but with the possibility to ask help from a coach on the initiative of the respondent (on demand, by email); (3) the same as 1, but with weekly scheduled contacts initiated by a coach (once per week, by email); (4) weekly scheduled contacts initiated by a coach, but no web-based intervention; (5) information only (through the internet). The interventions will consist of five weekly lessons. Primary outcome measures are symptoms of depression and anxiety. Secondary outcome measures are drop-out from the intervention, quality of life, and economic costs. Other secondary outcome measures that may predict outcome are also studied, e.g. client satisfaction and problem-solving skills. Measures are taken at baseline (pre-test), directly after the intervention (post-test, five weeks after baseline), 3 months later, and 12 months later. Analysis will be conducted on the intention-to-treat sample.

**Discussion:**

This study aims to provide more insight into the clinical effectiveness, differences in drop-out rate and costs between interventions with and without support, and in particular different levels of support. This is important to know in relation to the dissemination of internet-based self-help interventions.

**Trial Registration:**

Nederlands Trial Register (NTR): TC1355

## Background

Depressive and anxiety disorders are highly prevalent among society [1,2] and responsible for high societal costs [3]. Therefore, effective and inexpensive treatments should be made readily available [4]. Despite its effectiveness [5,6], only a small number of people receive psychological treatment by a properly trained mental health professional. Several reasons can account for this, such as long waiting lists, high costs [7] and limited accessibility [4].

Internet usage increased rapidly among the world population by over 300% [8] over the past eight years, with a population coverage of 48% to 78% in the Western countries. As much as 35% to 80% of users consult the internet for health care purposes [9]. This trend creates new opportunities for health care providers to reach their target population, for example via online mental health treatment.

Internet-based self-help interventions are standardized psychological treatments provided online, in which a patient can help him- or herself, either independently or with the help of a (professional) therapist. The support given by a therapist or coach can vary from more personalized extensive written input [10] to minimal contact [11]. Several well-designed randomized controlled trials report that internet-based self-help interventions for mild depression and anxiety are effective in reducing these symptoms [12,13]. It can be expected, therefore, that the use of (guided) self-help through the internet will be increasingly used in the prevention of common mental disorders. Advantages of these kinds of treatments are, for example, the reduced therapist time [14], reduced costs [7] and the ability to reach populations with mood and anxiety disorders who are not reached with more traditional forms of treatment [15].

Although the efficacy of internet-based self-help has been demonstrated sufficiently, it is not clear how these interventions should be offered to the population who can benefit from it. A major issue, for example, is whether it is better to offer the intervention with the support of a coach or if automated programs could work. In case support is necessary, it is not clear which level of support is needed. One of the advantages of a system without a coach is the ease and low costs of implementation, as it does not require a complex and costly structure of professionals. Furthermore, there is virtually no limit as to how many clients can enter the program, since additional clients will not imply additional therapist time [4]. On the other hand, a system organization, in which participants have to be assigned to coaches, will account for high costs and is more difficult to organize, since the coaches have to be trained, have to have sufficient time and have to be paid. There will also be limits on the amount of participants entering the program. However, legal and ethical issues of unguided programs (e.g., disappointment if the treatment fails, and the question of responsibility), the necessary risks of failing to identify cases for whom pure self-help is not enough, and the inability to monitor patients and adjust their treatment when necessary (e.g., in crisis situations) are arguments against unguided programs.

There is evidence that in interventions without a coach, compared to interventions with a coach, the drop-out rate is considerably higher [12]. Moreover, although interventions without a coach can be effective in reducing depressive and anxiety symptoms, they are associated with much smaller effect sizes than interventions in which the user had regular contact with a coach [12]. How large the differences in effectiveness are between interventions with and those without a coach has not been sufficiently studied. Moreover, it has not been examined whether there are differences in drop-out rate and costs between interventions with and without support, and in particular different levels of support. The aim of this study is to examine whether an internet-based self-help intervention with a coach is more effective than the same intervention without a coach in terms of clinical outcomes, drop-out and economic costs. Furthermore, this study examines which level of support by a coach is more effective compared to other levels of support.

## Methods

### Study design

This study is a randomized controlled trial with three active treatments with different levels of support and two control conditions (general support by coach and information only). The three active treatment and control conditions are:

1. *Web-PS*: Brief internet-based **p**roblem-**s**olving on the internet ('self-examination' treatment, see below) without coaching (but with automated emails at regular times).

2. *Web-PS + c*: The same as in 1, but with the possibility for subjects on their own initiative to email a **c**oach asking for support.

3. *Web-PS + C *The same as in 1, but with a coach who will actively approach the subject at regular pre-agreed times (once per week, by email).

4. *C*: No internet intervention, but a **c**oach will approach the subject at regular pre-agreed times (once per week, by email or chat) to discuss problems and give general support (non-specific intervention).

5. *Web-info*: Only information on depression and anxiety (on the internet).

The non-specific intervention condition (condition 4) is added to control for the non-specific effects of coaching. The study protocol, information brochure and informed consent were approved by the Medical Ethics Committee of the VU University Medical Center (registration number 2008-011).

### Inclusion and exclusion criteria

Participants who return the informed consent will be included in the study if they: 1) are 18 years or older; 2) have symptoms of depression and/or anxiety (as defined by scoring above the cut-off of 16 on the Center for Epidemiological Studies Depression scale (CES-D) and eight on the Hospital Anxiety and Depression Scale (HADS); 3) which are not too severe (1 standard deviation above the population mean on the CES-D, cut-off < 39 and/or HADS cut-off <15 [16,17]), 4) have access to a computer with a fast internet connection and 5) have sufficient knowledge of the Dutch language. Excluded are subjects with severe depressive or anxiety disorders (score ≥ 39 on the CES-D; ≥ 15 on HADS), active suicidal plans (≥ 3 SQ suicide) and/or currently under treatment by a mental health specialist. Participants will not be excluded if they are taking prescribed medicine for anxiety or depressive disorders over one month with stable dosage.

### Recruitment

A total of 500 participants with mild to moderate depression and/or anxiety will be recruited from the general population through banners on internet websites (Google, Dutch internet-sites on mental health issues), as well as local newspapers. All advertisements are in Dutch. In choosing the websites specific attention will be paid to include patients with different ethnic backgrounds and socioeconomic groups. In these banners, a link to a website is given which contains information about the study. Patients can leave their names and email address when interested in the study. More extensive information will then be sent by post, together with an informed consent form and a link by e-mail to the online baseline-questionnaire. Subjects who meet the inclusion criteria (as described above) will be randomized to the different treatment arms and will be notified by email. Subjects who are excluded will be notified by email and advised to contact their GP when their symptoms of depression or anxiety are severe (as determined by the CES-D and HADS). For practical reasons, recruitment will take place in batches of 100 participants.

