### Assessments

Primary outcome measures are symptoms of depression and anxiety. Secondary outcome measures are drop-out from the intervention, quality of life, and economic costs. Other secondary outcome measures that may predict outcome are also studied, e.g. client satisfaction and problem-solving skills. Measures are taken at baseline (pre-test), directly after the intervention (post-test, five weeks after baseline), three months later, and 12 months later. All measurements are self report measures and will be administered through the internet.

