#### Suicidal intentions

To measure suicidal intentions of participants we use one question of the screening questionnaire (SQ), a quick self-report developed by Marks et al. [51]. Likert-scale response options are used, total score ranges from 0 to 3, cut off score is above 3.

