This study has several limitations. First, there could be selective drop-out in the non-internet-intervention groups (control condition 4: support only; control condition 5: only information). In the analysis, we will examine whether this happened. Furthermore, we will make use of intention-to-treat analysis, in which missing values are estimated with different techniques (e.g., multiple regression, multiple imputation). Second, the control group receives information only, which can be effective in reducing symptoms of depression and anxiety, although effect sizes are small [11]. Third, psychometric properties of some of the questionnaires used in this study are not yet tested for online use, although this can be different from its paper-pencil versions [55]. One of the reasons is that people sometimes disclose more sensitive information in computer-based compared to face-to-face interviews [56]. A final limitation of this study concerns the sole use of self-rated instruments as outcome measures and the lack of a diagnostic interview; hence we have no knowledge whether subjects meet the criteria for a DSM-IV diagnosis of depression or anxiety. The lack of the gold standard of diagnosing makes it difficult to compare with other studies. However, since this preventive intervention is aimed to be applicable and accessible for a broad population of people from the community with clinically relevant symptoms of depression and anxiety [19], a formal diagnosis will not be necessary for participants to enter the program.

One of the strengths of this study concerns the formal evaluation of the cost effectiveness for the different levels of support given in the intervention, which has not been studied sufficiently previously [4]. Furthermore, by including the condition in which no intervention is given but only support of a coach, we will be able to examine the non-specific effects of coaching. Finally, external validity is a strong aspect of this study, since specific attention is given in the recruitment process to include patients with different ethnic backgrounds and socioeconomic groups.

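### The stated trigger for GP advice to excluded applicants uses only the CES-D and HADS, so it misses an applicant excluded on the suicide item alone

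*Protocol article*

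**What the plan says.** The Inclusion and exclusion criteria give three grounds for exclusion. The first is severity: "Excluded are subjects with severe depressive or anxiety disorders (score ≥ 39 on the CES-D; ≥ 15 on HADS"). The other two follow in the same sentence: "active suicidal plans (≥ 3 SQ suicide) and/or currently under treatment by a mental health specialist".

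The Recruitment section then says what happens to people who are screened out. They are notified by email and "advised to contact their GP when their symptoms of depression or anxiety are severe (as determined by the CES-D and HADS").

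The Suicidal intentions entry under Instruments shows that the suicide criterion has its own source: "To measure suicidal intentions of participants we use one question of the screening questionnaire (SQ"). It is not an item or subscale of the CES-D or the HADS.

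On how screening is done, the Assessments section says: "All measurements are self report measures and will be administered through the internet". The Discussion lists as a limitation "the sole use of self-rated instruments as outcome measures and the lack of a diagnostic interview".

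**The concern.** Two of the three exclusion grounds signal clinical risk: severe symptoms and active suicidal plans. The advice rule covers the first and not the second. Its parenthesis matters. Without it, suicidal plans could be read as a severe depressive symptom. With it, severity is decided by two named scales, and the suicide item plays no part.

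This is a matter of patient safety. Staff, or an automated email built from this sentence, would send a person with a CES-D of 39 to the GP. They would not be prompted to do so for a person with active suicidal plans and moderate scale scores. The article shows no other contact with that person after screening. Someone excluded on the suicide item alone is also, by the article's own criteria, not in current treatment with a mental health specialist, because that is a separate exclusion.

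**Working it through.** No estimate, power figure or sample size is involved. The check sets the exclusion rule beside the advice rule.

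**Inputs**

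- Severity thresholds: CES-D 39 or more, HADS 15 or more (Inclusion and exclusion criteria).
- Suicide exclusion: SQ suicide item 3 or more (same section).
- Trigger for GP advice: severe symptoms as judged on the CES-D and HADS (Recruitment).

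**Applying the rules to four applicants** (illustrative scores; none is under specialist treatment; severe is read as reaching the threshold on either scale)

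| CES-D | HADS | SQ suicide | Excluded? | Advice condition met? |
|---|---|---|---|---|
| 39 | 10 | 0 | Yes, severity | Yes |
| 30 | 15 | 0 | Yes, severity | Yes |
| 39 | 10 | 3 | Yes, severity and suicide item | Yes, through the CES-D |
| 30 | 10 | 3 | Yes, suicide item only | **No** |

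In the last row the CES-D is 39 − 30 = 9 points below its severe threshold and the HADS is 15 − 10 = 5 points below its own. Neither scale is severe, so the condition fails. The third row shows that a suicidal applicant is covered only when a scale score happens to be severe as well.

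**Extent.** The condition fails whenever SQ suicide is 3 or more, CES-D is below 39 and HADS is below 15. Those upper limits are the ones the trial sets for entry, so the gap includes the whole severity range it recruits.

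**Is the gap closed elsewhere in the article?**

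- Suicidality appears only in the Inclusion and exclusion criteria and in the Suicidal intentions entry. Neither attaches an action to a positive answer.
- Advice to contact the GP appears only in Recruitment.
- Table 1 lists the SQ for motivation only.
- Coaching belongs to the trial conditions, so it does not reach someone excluded before randomization.
- Measurement is online self-report and the exclusion notice is an email.

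**A related inconsistency.** The Suicidal intentions entry describes the item as "total score ranges from 0 to 3, cut off score is above 3". No one can score above 3 on that range, so under this wording nobody would be excluded on the item and the group discussed here would be empty. The exclusion criteria use 3 or more, which can be reached and is the operative rule. This check rests on it.

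**The case against.** The strongest reply is that this is a condensed article. How staff respond to a positive suicide screen is operational detail that usually sits in the full protocol. The Study design section says an ethics committee approved a protocol, brochure and consent form, and the full protocol is not shown here. The Recruitment sentence says when advice is given, not that it is given only then, so it denies advice to nobody. The harm arises only if no fuller procedure exists, and that cannot be known from the article.

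Much of this stands. The absence of a suicide-risk procedure from the article does not show that none exists, and the sentence is not exclusive. The Discussion's remark on the missing diagnostic interview concerns outcome measurement and comparability with other studies. It is weak evidence about contact after screening; at most it confirms that no interview is part of the assessments. The example scores are invented, the number of people affected is unknown, and the trial's results are untouched because these people are never randomized. The conflicting cut-off in the Suicidal intentions entry is a separate error that also needs correcting.

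The reply does not remove the point. The article does not leave referral to another document. It states who is excluded, how they are told, when they get GP advice and which instruments decide. A rule spelled out to that degree can be judged as written, and as written it prompts advice for a high CES-D score and not for active suicidal plans.

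**Conclusion.** The concern holds. The advice condition leaves out every applicant excluded on the SQ suicide item whose CES-D is below 39 and HADS below 15. How many people that is cannot be estimated from the article.

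The conclusion assumes that the operative suicide threshold is the one in the exclusion criteria (3 or more), and that severity means the CES-D and HADS thresholds given there. It is limited to the wording of the rule and does not claim that suicidal applicants went without advice. Confidence is medium because a fuller document may already deal with this group. Even so, the sentence should be corrected: the possible consequence is a missed prompt to refer a suicidal person, and the change costs almost nothing.

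**What to change.** Extend the Recruitment sentence and the exclusion email so that advice to contact the GP also goes to anyone excluded on the SQ suicide item at 3 or more, whatever their CES-D and HADS scores. If a suicide-risk procedure for these applicants already exists in a fuller document, refer to it in that sentence instead. Bring the cut-off in the Suicidal intentions entry into line with the exclusion criteria at the same time, so that the added condition points to a single threshold.

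The cost is one added condition in one sentence and in one email, and possibly a little staff time. Eligibility, randomization, outcomes, sample size and analysis stay as they are.

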### Randomization

Based on three factors (depression and anxiety scores, prescribed medication for anxiety or depression), participants will be randomized after the baseline measurement. Subjects will be randomized into five groups (the three active treatment conditions and two control conditions) using block randomization with variable sizes. The allocation schedule will be made with a computerized random number generator by an independent researcher and will be unknown to the investigators.

### Interventions

#### Problem-Solving Treatment

The intervention used in this study for conditions 1–3 is a brief, web-based intervention for problem-solving, called "allesondercontrole", based on self-examination therapy (SET [18]). In problem solving therapy (PST), it is assumed that depressive and anxiety symptoms can be caused by practical problems people face in their daily lives. When people can resolve their problems, their symptoms of depression and anxiety will decrease. During PST an individual learns a specific problem-solving procedure in an attempt to resolve their problems' in a structured way [19]. "Allesondercontrole" is expanded with more information, examples, exercise and forms and consists of five weekly lessons. Participants are allowed to use the program 24/7 as long and often as they want during the trial period. See Warmerdam et al. [19] for a more elaborate description of "allesondercontrole". This website is already available (currently only available for research purposes) and proved to be effective in both international and national research for depression and anxiety [13,18-21].

#### Control groups

The participants in control condition four (only coaching, no internet intervention) receive non-directive support by their coach for a maximum of 15 minutes per week. The support consists of non-directive conversation skill techniques based on Client-centered Therapy [22], communication skills [23] and clinical management used in the National Institute of Mental Health (NIMH) treatment for adolescents with depression study (TADS) [24]. The coach is allowed to give general support only, while at the same time avoiding specific techniques from other formal psychotherapeutic interventions. Participants can choose between emailing or chatting with their coach. Participants will receive the "allesondercontrole" intervention in a self-help book-form [25] six weeks after entering the study. The participants in the control condition five only get 24/7 access to a website with general information about depression and anxiety. The participants in this condition are offered the intervention 6 weeks after entering the study.

#### Support

In condition one, automated standardized emails are sent to subjects with additional information regarding how to make the exercises. There will be no support from a coach.

In condition two, the respondent has the option to contact the coach by email for additional support and in condition three, the coach will actively approach the respondents per email, once per week. This will take 10 to 15 minutes per week; total coaching time is estimated at one to 1.5 hours per respondent [13]. Coaching is only meant to give support in working through the self-help method and not aimed at developing a patient-therapist relation. The participants in condition four receive non-directive support by their coach via email or chat. Coaching will be given by Master level students in clinical psychology. Coaches for condition 2 and 3 will receive a training of approximately six hours given by the first and second author of this article. The training will consist of reading the interventions materials themselves, carrying out assignments, and practicing feedback to each other by e-mail. During the training they will also practice with case material and their feedback will be discussed. The training for condition four, non-directive support, will be given by the first author of this article and consists of carrying out assignments and practicing non-directive conversation skills for approximately four hours.

In all five conditions two automated emails will be send to participants reminding them about when they can fill in the post-test measurement. Based on a recent study of Nordin et al. [Nordin S, Carlbring P, Cuijpers P, & Andersson, G: Expanding the limits of bibliotherapy for panic disorder. Randomized trial of self-help without support but with a clear deadline, submitted], we expect participants to adhere better to the program when they are aware of a deadline, in which their symptoms are surveyed.

